## Assignment of interventions: blinding

### Who will be blinded {17a}

According to the allocation procedures (16a–c), the key study personnel and the patients were blinded. The authors of the final statistical analysis plan (e.g., principal investigators, statisticians) will be blinded concerning the therapy allocation of the patients but not to all other final data in order to establish a blinded review of the data before the start of the final analysis.

### Procedure for unblinding if needed {17b}

Unblinding is permissible in cases of emergency. Envelopes for emergency unblinding are available for the respective patient in the study medication package. Opening of an unblinding envelope must be documented.

## Data collection and management

### Plans for assessment and collection of outcomes {18a}

#### Hearing evaluation

##### Change in pure tone hearing threshold.

To evaluate the success of therapy, psychoacoustic hearing tests (audiometry) will be used to measure the change in the average pure tone hearing thresholds of the three adjacent audiometric frequencies (within a range of 0.25–8 kHz: 250 Hz, 500 Hz, 1 kHz, 1.5 kHz, 2 kHz, 3 kHz, 4 kHz, 6 kHz, 8 kHz) that are most affected by the ISSHL. The three most affected frequencies are identified by calculating the difference between the actual hearing threshold and the hearing threshold at the specific frequency from the reference audiogram. The reference audiogram is defined as (1) the pre-event audiogram, and, if not available (2) the audiogram of the unaffected ear, or, if also not available or applicable, (3) the ISO 7029 age- and sex-corrected standard audiogram. The three-frequency combination with the largest difference to the reference audiogram will be determined. The proportions of patients who completely recover, partially recover, do not at all recover their hearing, or with worsening of hearing will be determined.

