#### Secondary outcomes

Speech understanding (especially in noise) reflects a patient’s ability to communicate in everyday and working life better than pure tone threshold. However, the results of speech audiometry in different languages cannot easily be compared and are also influenced by other parameters such as speech competence. Speech audiometry tests are also difficult to interpret in patients whose native language is not that of the test lists.

Different categories of improvement based on change in pure tone or speech reception threshold have been suggested (e.g., [4, 13, 17, 36, 38] among others). A clinical practice guideline recognizes that fixed levels of improvement “… may have different benefits for different patients …” [38]. Therefore, speech audiometry and categories of improvement will be used as secondary outcome measures in this study. The recovery category is defined based on the pure tone average 30 days after start of therapy and referenced to the pre-event audiogram, the audiogram of the unaffected ear, or the ISO age- and sex-corrected standard audiogram: deterioration (> 10 dB increase, i.e., worsening), no change (≤ ±10 dB change), partial recovery (> 10 dB increase, i.e., improvement but not ≤ 10 dB difference to reference audiogram), and complete recovery (≤ 10 dB difference to reference audiogram). Most international trials and classifications of hearing improvement use 10 dB as a criterion for “partial improvement” (summary in [29], recommendation in [38]). The 10-dB criterion is based on the 5‑dB resolution of the method (ISO 8253-1), the test-retest reliability, and the clinical relevance of the hearing improvement.

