### Sample size {14}

This three-armed trial (randomization ratio: 1:1:1) is aimed at comparing standard-dose systemic therapy with two types of high doses of systemic therapy concerning the primary endpoint using two individual statistical tests assuming a normal distribution of the primary endpoint in the population. For a global significance level of 0.05, we adjust for two tests using a local level for each test of 0.025. The following assumptions are based on the available literature [32]. A sample size of 88 in each group will have 80% power to detect a difference between high dose and standard dose, when the true difference in means is −10.0 (e.g., the difference between a group 1 mean, μ1, of 30.7 and a group 2 mean, μ2, of 40.7) assuming that the common standard deviation is 21.3. The sample size calculation was performed for two-sample *t* tests with nQuery Version 7.0. Assuming a dropout rate of approximately 15%, a total of 312 patients need to be randomized (1:1:1) to maintain at least 264 evaluable patients with complete data (high-dose dexamethasone: 104; high-dose prednisolone: 104, standard prednisolone: 104).

Systemic glucocorticoids are the standard treatment in ISSHL. Since the study drugs thus do not involve a completely new therapeutic concept, patient compliance is generally estimated as high. We assume a rate of loss to follow-up of 15%. This estimate is based on two recent RCTs on ISSHL. Nosrati-Zarenoe and Hultrantz (2012) randomized 103 patients and were able to analyze 88 (85%) on day 8 of the assessment and 73 (71%) at the 3‑month time point [26]. In the study of Rauch et al. (2011), 221 of 255 patients (87%) completed the intervention and 2‑month follow-up (per-protocol analysis [32]).

The trial will be analyzed according to the intention-to-treat principle including all randomized patients. A per-protocol analysis will be performed as sensitivity analysis.

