## Statistical methods

### Statistical methods for primary and secondary outcomes {20a}

The primary confirmatory analyses will be based on the intention-to-treat population (ITT), which will include all randomized patients. The analysis will be done according to the intention-to-treat principle; this means every patient remains in the treatment group as allocated by randomization. The per-protocol population (PP) will be formed from the ITT. Only patients with major protocol violations will be excluded. The details will be described in the final statistical analysis plan.

The PP will be the secondary analysis population for PP analysis to confirm the results of the ITT analysis.

The confirmatory analysis of the primary endpoint is planned after complete documentation and data cleaning including visit 9. The confirmatory analysis aims on showing the superiority of one or both of the high-dose treatments in comparison with the standard therapy. Therefore, two analyses of covariance (adjusted for baseline PTA) will be performed at a local significance level of α = 0.025 (two sided), which means for a global significance level of α = 0.05 (two sided) for the statistical evaluation of the primary endpoint.

The differences in the primary endpoint between the high-dose groups and the standard group will be estimated with 97.5% confidence intervals (being confirmatory and consistent to the test procedure) and with 95% confidence intervals (being comparable to results usually presented in the literature).

The sample size of the study was planned to achieve a high power for the comparisons of high dose vs. standard dose. But, if superiority of both high-dose treatments versus the standard treatment can be shown, both high-dose treatment arms will be compared at a significance level of α = 0.05 (two sided) and the difference will be estimated with 95% confidence interval as a secondary objective.

The data of the ITT and PP will be statistically described in detail. This includes:Listings of all documented data for every patient.Summary tables of all variables. Discrete variables will be described by absolute and relative frequencies. Continuous variables will be described by statistical characteristics (minimum, maximum, quartiles, median, mean, standard deviation).

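### The confirmatory ANCOVAs omit the reference-audiogram threshold that every patient has, which may forgo a modest amount of precision

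*Protocol article*

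**What the plan says.** The primary endpoint is the change, 30 days after the start of therapy, in the average threshold of the three contiguous frequencies most affected (Primary outcome; section 18a). Section 18a states how they are found: "The three most affected frequencies are identified by calculating the difference between the actual hearing threshold and the hearing threshold at the specific frequency" in the reference audiogram. The reference is the pre-event audiogram, failing that the unaffected ear, failing that the ISO 7029 norm, so a value always exists. Eligibility also requires an initial loss of at least 30 dB against a comparator of this kind, and an absolute average of at least 50 dB HL.

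The secondary recovery categories are also "referenced to the pre-event audiogram, the audiogram of the unaffected ear, or the ISO age- and sex-corrected standard audiogram", with complete recovery meaning a result within 10 dB of that reference.

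For the primary endpoint, section 20a says that "two analyses of covariance (adjusted for baseline PTA) will be performed at a local significance level" of 0.025, two-sided. Randomization is stratified on the same variable, cut at 81 dB. Section 20a also says that the confirmatory analyses were fully specified in the protocol and leaves other details to the SAP. The covariate set is therefore a stated choice and has not been deferred.

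**The concern.** Baseline PTA is the sum of the reference threshold and the new loss, and the two parts bear differently on the endpoint. More new loss leaves more to regain; a worse reference, at the same baseline PTA, leaves less. A model with baseline PTA alone cannot separate them.

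Take two eligible ears, both at 80 dB. With a reference of 10 dB there are about 70 dB to regain; with a reference of 50 dB, about 30 dB. The planned ANCOVA gives both the same expected change. If the reference predicts change beyond baseline PTA, that predictable part stays in the error term and widens both confirmatory confidence intervals.

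Only precision is at stake. Recruitment has closed (Discussion), so further precision can come only from the analysis.

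**Working it through.** **1. The plan's own figure.** Section 14 states: "A sample size of 88 in each group will have 80% power to detect a difference between high dose and standard dose". Its inputs are a mean difference of 10 dB, an SD of 21.3 dB in both groups and, for multiplicity, a halved level: "we adjust for two tests using a local level for each test of 0.025". For a two-sample t test the standard error is 21.3 × √(2/88) = 3.21 dB and the noncentrality is 10/3.21 = 3.11. With 174 degrees of freedom and two-sided 0.025, power is 80.2%. At 87 per arm it is 79.7%, so 88 reproduces. Then 88/0.85 rounds up to 104 per arm, 312 in total.

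**2. Does the limit matter in the planned range?** The planning means are "a group 1 mean, μ1, of 30.7 and a group 2 mean, μ2, of 40.7". Read as dB of improvement (an assumption, since the endpoint is a change), both exceed the smallest eligible initial loss of 30 dB. A patient near the entry limit would not reach either mean by returning to the reference.

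**3. Why the reference may predict change.** Let B be baseline PTA, R reference PTA and f the recovered fraction. Then change = f × (B − R) plus noise. If f is unrelated to B and R, expected change at fixed B falls by E(f) for each dB of R. If f falls as the loss grows, the dependence weakens. With mean f = 0.55 and mean loss 55 dB (both assumed), the slope of expected change on loss at the mean is:
- f constant: 0.55
- f lower by 0.03 per 10 dB: 0.55 − 0.003 × 55 = 0.385
- f lower by 0.05 per 10 dB: 0.55 − 0.005 × 55 = 0.275
- f lower by 0.07 per 10 dB: 0.55 − 0.007 × 55 = 0.165

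**4. Size of the variance reduction (simulated; all inputs assumed).** Initial loss N(55, 18); reference mean 22 dB; U-shaped recovered fraction with mean 0.55; 110 dB ceiling; 4 dB measurement noise; the article's entry limits. Reduction in the variance left after baseline PTA when R is added:

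| Recovered fraction | Reference SD 8 | SD 12 | SD 16 |
|---|---|---|---|
| independent of loss | 3.5% | 6.1% | 8.4% |
| 3 points lower per 10 dB more loss | 1.5% | 2.6% | 3.6% |
| 5 points lower per 10 dB | 0.6% | 1.1% | 1.5% |
| 7 points lower per 10 dB | 0.1 to 0.3% across all three | | |

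With 8 dB of proxy error in the reference, the first row falls from 3.5% to 1.5% and from 6.1% to 3.5%. Other plausible inputs, still with the fraction independent of loss, gave 4 to 12%. Scenarios with high recovery (mean fraction 0.67) gave 22 to 29%, but their SD of change was 16.4 to 16.7 dB, well below the planned 21.3, so they are left out of the range.

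**5. Conversion to power.** Residual SD = 21.3 × √(1 − r), where r is the variance reduction. At 88 per arm:

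| r | Residual SD | Power | 97.5% CI half-width |
|---|---|---|---|
| 0 | 21.3 | 80.2% | 7.26 dB |
| 0.05 | 20.8 | 82.4% | 7.08 dB |
| 0.10 | 20.2 | 84.6% | 6.89 dB |
| 0.12 | 20.0 | 85.4% | 6.81 dB |

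This takes 21.3 as the SD after adjustment for baseline PTA, although section 14 gives it for an unadjusted t test. If it is the unadjusted SD, the planned ANCOVA already exceeds 80% and the added points are somewhat fewer.

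**The case against.** The strongest reply is that nothing here is wrong. Adjusting a change score for its own baseline, with randomization stratified on the same variable, is standard and consistent. The trial was sized on an unadjusted test, so any covariate gain comes on top of a target already met. That stands: this is a point about efficiency.

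The gain is also assumption-driven. No document gives the spread of reference thresholds, the recovered fraction or a partial correlation. The article itself treats baseline severity as possibly prognostic or predictive, so a recovered fraction that varies with loss is a live possibility, and a modest dependence removes most of the benefit. That stands too, and is why the range starts at zero.

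A change now is not free. The protocol calls its confirmatory analyses fully specified, and the SAP authors can see all data except allocation during the blind review (section 17a; Trial status). Changing the model then needs a documented reason. This argues for a recorded change with the protocol's model still reported; it does not rule the change out, because allocation is still concealed.

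Finally, the recovery categories already use the reference. They are secondary and descriptive, and do nothing for the precision of the primary contrasts.

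**Conclusion.** The point holds as a modest, optional gain in precision. A baseline value that exists for every patient, at the endpoint frequencies, and that the article itself uses as the yardstick of complete recovery, is absent from the confirmatory model. Under the assumptions shown, including it cuts residual variance by about 0 to 12% and adds about 0 to 5 points of power at 88 per arm. The upper end needs a recovered fraction unrelated to the size of the loss and a reference that measures prior hearing well.

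Three stronger readings are not supported. A reader might infer that the planned analysis is biased or inflates type I error; under randomization, leaving out a prognostic covariate from this ANCOVA does neither. A reader might infer that the outcome is strictly capped at the initial loss; the unaffected ear and the ISO norm only stand in for prior hearing, and retest error allows overshoot, so the limit is approximate. A reader might infer that the trial is underpowered, or that the omission equals a definite number of patients; the stated 80% reproduces, and the documents hold no figure from which such a number could be derived.

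**What to change.** Before unblinding, record a change to the protocol or SAP that specifies both confirmatory ANCOVAs as change in three-frequency PTA on treatment, baseline PTA and reference-audiogram PTA at the same three frequencies. Entering initial loss instead of reference PTA, alongside baseline PTA, gives the same treatment estimate. State the reason (the reference approximately limits regainable hearing) and that allocation was still concealed. Report the protocol's baseline-PTA-only model alongside.

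The cost is one degree of freedom, a short SAP entry and a documented departure from a model described as fully specified. No new data are needed, because the reference thresholds are already required to select the frequencies.

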##### Assessment of communication ability.

Speech intelligibility is measured specifically for each ear according to ISO 8253‑3 with two lists of the German Freiburger monosyllables test determining the percentage of monosyllables understood at 65 dB and 80 dB SPL, respectively. Furthermore, the proportion of patients who receive or are recommended to receive a conventional hearing aid or a cochlear implant after the treatment will be determined.

##### Assessment of quality of life.

Quality of life is assessed using the HHIE (Hearing Handicap Inventory for the Elderly) and SF 12 questionnaires, which must be completed by the patients themselves. This makes it clear to what extent the treatment in a therapy arm has led to a particular subjective improvement in the patient.

##### Tinnitus assessment.

The presence and severity of tinnitus are assessed with visual analog scales.

##### Evaluation of “rescue therapy.”

The proportion of patients who will receive any form of “rescue therapy” (outside the study protocol) is determined.

#### Assessments of systemic safety aspects

##### Blood pressure.

Long-term blood pressure measurement (24 h) is performed at the study centers on day 5 (±2 days). The pseudonymized measurement protocols (printout of the measured value lists) are transmitted to the coordinating center to enable evaluation under consideration of the technical quality. Therefore, the following criteria will be applied: at least nine complete measurements are required during daytime (06.00–22.00 h) and six during nighttime (22.00–06.00 h). If the standard deviation of the measurements in one of these time sections is > 25%, the measurements will be checked manually for validity. The circadian rhythm will be evaluated based on the difference between day- and nighttime average systolic pressure. If the nighttime average is ≥ 10% lower than the daytime average, the patient is categorized as a “dipper,” otherwise as a “non-dipper.”

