**Fig. 1 Fig1:**
[figure not shown]
Intervention scheme. *HD* high dose, *ISSHL* idiopathic sudden sensorineural hearing loss, *i.v.* intravenous, *p.o.* per os. ^a^Randomization and first study medication intake/injection may be on same day

The participants will be randomized equally to one of the three treatment groups (one control, two interventions) according to the following treatment schemes:Intervention 1: 5 days of 250 mg/day prednisolone-21-hydrogen succinate, sodium salt intravenously (+ placebo p.o. 10 days)Intervention 2: 5 days of 40 mg/day dexamethasone orally (+ placebo i.v. 5 days/p.o. 5 days)Control: 60 mg prednisolone orally for 5 days followed by five tapering doses (+ placebo i.v. 5 days)

Patients will be followed up for 30 days after randomization for primary and secondary endpoints as well as safety parameters and for 6 months after randomization for additional secondary endpoints with relevance for patients.

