Arterial hypertension and impaired glucose tolerance are the two major adverse events following short-term high-dose glucocorticoid treatment. Alterations in glucose metabolism arise from enhanced hepatic gluconeogenesis and impaired glucose uptake by adipose tissues [35]. In healthy individuals, this rarely leads to relevant complications. However, in the presence of already impaired glucose tolerance, hyperglycemia may occur. The HOMA-IR is a useful index for detecting subclinical insulin resistance, which is more sensitive for detecting altered glucose metabolism than mere measurements of blood glucose [2].

Blood pressure effects of glucocorticoids are in part mediated by renal fluid retention and increased vascular responsiveness to catecholamines; however, additional unknown mechanisms seem to be involved [42]. Blood pressure elevations will be detected by 24‑h blood pressure measurements on day 5 of glucocorticoid treatment, where maximum effects are expected.

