^3^ Central laboratory evaluations: measurement of HbA1c (baseline only), insulin, HOMA-IR (baseline and V6), fasting if possible, blood sample must be taken before medication; if V6 Saturday or Sunday or holiday: blood sample may be taken at last or next working day

^4^ Pure tone audiogram 250–8000 Hz, bone and air conduction; impedance audiometry, speech (monosyllables at 65 and 80 dB SPL with Freiburger speech test)

^5^ If visit on Saturday, Sunday or holiday these assessments may be omitted

^6^ Includes: spontaneous nystagmus, caloric or head impulse test, Romberg test; may be done at V1 or V2, at V2 also after medication possible

^7^ Day 5 ± 2 days

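### The 24-h blood pressure window allows recordings on days 6–7, when the high-dose arms are off active drug and control is still on its taper; the insulin/HOMA-IR sample shares this only from day 7

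*Protocol article*

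**What the plan says.** **Dosing** (Protocol article, Intervention description {11a} and the treatment schemes under Fig. 1):

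- Intervention 1: "5 days of 250 mg/day prednisolone-21-hydrogen succinate, sodium salt intravenously (+ placebo p.o. 10 days".
- Intervention 2: "5 days of 40 mg/day dexamethasone orally (+ placebo i.v. 5 days/p.o. 5 days".
- Control: "60 mg prednisolone orally for 5 days followed by five tapering doses".
- The text adds that the high-dose treatments end without a taper.

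**24-h blood pressure.** The Blood pressure section says that the recording "is performed at the study centers on day 5 (±2 days", and Table 2, footnote 7, gives the same tolerance. Table 2 schedules it once, at visit 6, with no baseline 24-h recording. The reason given under Secondary outcomes is that elevations will be detected "on day 5 of glucocorticoid treatment, where maximum effects are expected".

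**Insulin/HOMA-IR.** The Glucose tolerance section places this measurement at baseline and on day 5 of therapy. Table 2, footnote 3, adds that the "blood sample must be taken before medication", and "if V6 Saturday or Sunday or holiday: blood sample may be taken at last or next working day".

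**Role of these outcomes.** The abstract names hyperglycemia and hypertension as the safety focus.

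**The concern.** The window is the same in every arm, but exposure inside it is not. Up to day 5 all three arms take active glucocorticoid. From day 6 the high-dose arms take placebo and the control arm takes tapering prednisolone. A recording begun on day 6 or 7 therefore does not compare high dose with standard dose on treatment. It compares recently stopped high dose with a continuing taper. Neither blinding nor identical windows removes this, because the same calendar day means different exposure by arm.

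If the pressor or metabolic effect fades after stopping, late measurements lower the high-dose arms relative to control. Pooling them with on-treatment measurements could then make high dose look safer than it is, on the two harms that the trial sets out to document. The 24-h endpoint is the more exposed, since it rests on one recording without a 24-h baseline.

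**Working it through.** The plan states no sample size, expected difference or power for blood pressure or glucose, so there is no figure of its own to reproduce here. Its sample size concerns the hearing endpoint and is not affected. The check has three steps.

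**1. Blood pressure: permitted days against dosing days**

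- Window: 5 − 2 = day 3 to 5 + 2 = day 7, so five permitted start days.
- Active drug in the high-dose arms: days 1–5.
- Active drug in control: days 1–5, then five tapering doses. The 10 days of oral placebo in intervention 1 imply days 6–10.
- Days 3, 4 and 5: all arms on active drug.
- Days 6 and 7: high-dose arms off active drug, control on its first and second tapering doses.

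Two of the five permitted start days have unequal exposure.

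**2. Visit 6 blood sample: which start days lead where**

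Visit 6 is four calendar days after day 1. Ignoring holidays:

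| Day 1 | Visit 6 | Last working day | Next working day |
|---|---|---|---|
| Tuesday | Saturday | Friday, day 4 | Monday, day 7 |
| Wednesday | Sunday | Friday, day 3 | Monday, day 6 |
| Any other day | Weekday | no shift | no shift |

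The sample precedes that day's medication. On day 6 it comes about one dosing interval after the fifth dose in every arm and before control's first tapering dose, so the arms are comparable. On day 7 control has already taken one tapering dose and the high-dose arms have had no active drug since day 5. Unequal exposure therefore needs a Tuesday start with the later option chosen, or a holiday. Assuming starts spread evenly over the days used, the ceiling is 1/7 = 14% (starts on all seven days) to 1/5 = 20% (weekday starts only), plus holidays.

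**3. What late measurement could do to the contrast (illustration)**

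Let f be the share measured late, h and c the on-drug effects in the high-dose and control arms, and r and s the fractions of those effects still present when measured late. Then

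observed / on-treatment contrast = [(1 − f)(h − c) + f(r·h − s·c)] / (h − c).

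If the late difference is zero, this reduces to 1 − f. With recordings spread evenly over days 3–7, f = 2/5 = 0.40 and the ratio is 0.60.

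A second set of assumed inputs is h = 1, c = 0.5, s = 0.8:

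| f | r = 0 | r = 0.5 | r = 1 |
|---|---|---|---|
| 0.20 | 0.64 | 0.84 | 1.04 |
| 0.40 | 0.28 | 0.68 | 1.08 |

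For example, f = 0.40 and r = 0 gives (0.60 × 0.5 + 0.40 × (0 − 0.4)) / 0.5 = 0.14 / 0.5 = 0.28.

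The contrast is diluted when r·h − s·c < h − c. With these inputs that means r < 0.9; above that it is slightly enlarged. None of f, h, c, r and s is given in the documents.

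**The case against.** **The blood sample can move either way, and before medication.** This stands. The sample may be drawn on the last working day as well as the next one, and the earlier option falls on day 3 or 4, when all arms are on drug. A reader might infer that every sample moved to the next working day is unbalanced, or that all patients with a weekend visit 6 (2/7 = 29% to 2/5 = 40%) are affected. The pre-medication rule and the earlier option do not support that; only day 7 or later matters.

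**Few recordings may actually be late.** This stands as a caution. Table 2 has visits on days 3, 4 and 5 and then none until days 10–13, so a start on day 6 or 7 would need an extra attendance. An even spread over the window is only an assumption. The window nevertheless permits these days, and the article gives no distribution of recording days.

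**A target day with a tolerance is not a contradiction.** This is partly right. Both places that state the window agree, and the rationale says only what is expected. But the rationale refers to a day of treatment, and for the high-dose arms the upper half of the window lies after treatment. The mismatch is in the reasoning rather than in two conflicting numbers.

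**Other safety data are unaffected.** This stands. Clinic blood pressure and bedside glucose are scheduled on each of days 1–5, adverse events are recorded to visit 8, and tests on secondary endpoints are descriptive. These limit the damage but do not replace 24-h pressure, dipper status or HOMA-IR.

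**This belongs in the analysis plan.** The handling does, and the analysis plan is not shown, so its silence cannot be inferred. The window, however, is fixed in the protocol, and pooling everything inside it can understate harm. That is a reason to settle the handling before unblinding.

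**Conclusion.** The concern holds in a limited form. The protocol permits the single 24-h recording on two start days (6 and 7) when both high-dose arms are off active drug and control is not, which does not fit its own reason for day 5. The insulin/HOMA-IR sample shares the problem only on day 7 or later: at most 14% to 20% of patients without holidays, under evenly spread starts, and fewer if sites used the earlier option.

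The exposure mismatch follows directly from the text. Its effect on the results does not. A reader might infer that the safety comparisons are biased against finding harm from high dose. The documents do not support this as a fact, because they give neither the share measured late nor how long the effects persist. If effects fade, the difference can be understated: to 60% of the on-treatment contrast with 40% late and no off-drug difference. Under the second set of assumptions the range is 28% to 108%. With nearly full persistence there is no dilution.

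**What to change.** The windows can no longer be changed, since the Trial status section reports that follow-up has ended. The same section describes blind review with the analysis plan still being finalized, so the handling can be set there before unblinding:

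- Derive the measurement day and the time since the last active dose for each 24-h recording and each visit 6 sample.
- Base the main 24-h blood pressure comparison on recordings begun on days 3–5, and the insulin/HOMA-IR comparison on samples up to and including pre-dose day 6.
- Show later measurements separately, and give the full window as a sensitivity analysis.
- Tabulate measurement day by arm. This also shows how many samples were drawn early, after fewer than the planned doses.
- Adjust 24-h blood pressure for the baseline clinic blood pressure already collected, as there is no baseline 24-h recording.
- Reconcile the day 5 statements under Secondary outcomes and Glucose tolerance with the windows in the Blood pressure section and Table 2, footnotes 3 and 7.

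No dosing or clinical rule is touched. The cost is two derived variables and some wording, with slightly fewer measurements and so somewhat wider intervals in the main safety comparison.
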